### Study setting and sample selection

Participants will be recruited from acute and community settings across LHD 1 and LHD 2, NSW, Australia. Research sites are listed below in Table 2.

**Table 2 Tab2:** Research sites

	Acute		Community	
	Intervention	Control	Intervention	Control
LHD 1	Geriatric Rehab Unit (LHD1**HIS**1)	Geriatric Rehab Unit (LHD1**HCS**3)	Public Community Health Centre (LHD1**CIS**5)	Public Community Health Centre (LHD1**CCS**7)
	Medical ward at Hospital (LHD1**HIS**2)	Medical ward at Hospital (LHD1**HCS**4)	Non-public Home and Community Care (LHD1**CIS**6)	Non-public Home and Community Care (LHD1**CCS**8)
LHD 2	Medical ward at Hospital (LHD2**HIS**9)	Medical ward at Hospital (LHD2**HCS**11)	Public Community Health Centre (LHD2**CIS**13)	Public Community Health Centre (LHD2**CCS**15)
	Medical ward at Hospital (LHD2**HIS**10)	Medical ward at Hospital (LHD2**HCS**12)	Non-public Home and Community Care Service (LHD2**CIS**14)	Non-public Home and Community Care Service (LHD2**CCS**16)

Note: Hospital Intervention Site (*HIS*), Hospital Control Site (*HCS*), Community Intervention Site (*CIS*), Community Control Site (*CCS*). One full-time RN for 2 wards in one hospital and one full-time RN for 2 community service providers at one setting are allocated in each LHD

The 16 research sites were pair-matched (eight intervention, eight control) and selection was based on admission rates, patient profile, number of deaths per month/year, average length of stay and number of referrals from/to hospital and community. To minimise potential contamination of intervention the sites chosen are geographically separated. Both public funded and non-public sites are involved in this research, to maximise the generalisability.

All newly admitted patients to a site listed as an ‘intervention site’ will be offered facilitated ACP conversations, and all other sites will continue to deliver usual care (control sites).

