### Sample size calculation

Power calculations were conducted to determine the sample size required to detect a change of at least 10% in the primary outcome; that being the proportion of completed NSW ACDs. Change was defined as the difference between the proportion at baseline, assumed to be 5% and at follow-up. Setting alpha at 5%, power at 80% and assuming a non-response rate of 25%, a sample size of 288 is needed (144 in intervention sites and 144 in control sites). Given an average admittance rate of at least 10 per week per site and over a six-month period, there is almost complete surety that the study will not be under-powered.

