#### Quantitative data analysis

Participant demographics and characteristics will be collected at each site and will be tabulated to show the distribution of participant characteristics between control and intervention sites (i.e. age, sex, primary reason for admission &/or chronic health condition). Continuous variables will be described by mean (standard deviation) if normally distributed and by median (interquartile range) otherwise. Categorical variables will be described by count (percentage). Group comparisons for continuous outcomes will be undertaken by either the Student t-test or Mann-Whitney U test. The Fisher’s Exact test will be used for categorical outcomes.

Baseline characteristics of study groups will be compared to assess similarity at study entry, thereby allowing for the identification of significant imbalances requiring adjustment during analysis. To account this and for clustering at the site level, multi-level regression models with mixed effects will be built to estimate interventional effect. For each model building process, variables found to be significantly associated with respective outcome measures in the univariable analysis at the 10% level will be retained in the final modelling.

As the primary predictor of interest, intervention effect will be forced into the multivariable modelling. Continuous outcome measures will be analysed using linear regression models. For binary outcome measures, analysis will be by binary logistic regression, while multinominal logistic regression will be used to analyse non-binary categorical measures. Model diagnostics will be conducted on all models.

All tests of significance will be set at 5%. Statistical analysis will be performed using Stata version 15.0 (StataCorp, College Station, TX, USA).

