## Discussion

Given the nature of study design, it is not possible to ensure that participants in this study will be representative of the entire population of people with chronic conditions and their SDMs. It is also possible that the exclusion of participants with chronic diseases other than listed may limit the generalisability. It is also important to acknowledge the limitations derived from the nature of self-reported interview and/or survey including response bias and social desirability bias which may lower reliability and validity. The findings from self-reported data will provide valuable insights to answer secondary outcomes measures. The study will be well powered to test the primary outcome measure and the cost-effectiveness calculations.

The benefits of ACP are well known. Patients’ wishes and preferences for care will be respected, and families and health professionals will be eased from the burden of decision-making on patients’ behalf. But more importantly, normalised ACP will promote the actual process of discussing end-of-life issues, leaving patients and families with an increased sense of feeling of cared for and understood. Furthermore, it will assist the uptake of ‘Planning ahead’ practices among people with chronic disease in acute and community settings.

To the Authors knowledge, NPT has not previously been used to develop, implement, and evaluate ACP for people with chronic diseases in acute and community settings. The evidence generated from this project will open a new level of understanding of end-of-life care needs of people and the meanings attached to ACP. It will also contribute to development of new best practice model to normalise ACP across acute and community settings, which is sustainable, transferable and scalable. The normalisation of ACP provides people with chronic diseases and their family, clinicians and policy makers with a feasible and essential opportunity to focus on what matters to people in life, at the end of life, and at the very end of life.

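### The 288-patient calculation makes no allowance for clustering in 16 sites, and admission volume alone cannot guarantee 80% power

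*Protocol article*

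**What the plan says.** All references are to the protocol article.

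- **Sample size calculation.** The target is to "detect a change of at least 10% in the primary outcome; that being the proportion of completed NSW ACDs", where change is "the difference between the proportion at baseline, assumed to be 5% and at follow-up". The result is given as: "Setting alpha at 5%, power at 80% and assuming a non-response rate of 25%, a sample size of 288 is needed", split as "144 in intervention sites and 144 in control sites". Sidedness, an ICC, a design effect and the number of sites do not appear. From an average of ten or more admissions a week at each site over six months, the section concludes that "there is almost complete surety that the study will not be under-powered".
- **Study setting and sample selection.** Sixteen sites are matched in pairs, eight intervention and eight control. Every new admission at an intervention site is offered the intervention. The note to Table 2 adds: "One full-time RN for 2 wards in one hospital".
- **Quantitative data analysis.** To account "for clustering at the site level, multi-level regression models with mixed effects will be built".
- **Discussion.** "The study will be well powered to test the primary outcome measure and the cost-effectiveness calculations".
- **Abstract and Data collection.** The 288 is described as a minimum. The audit looks for ACP evidence in the records of everyone admitted to the sites in the audit periods, and consent is sought only before the content is read.

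**The concern.** Patients at one site share staff, routines and case mix, so their outcomes are correlated. The analysis section accepts this, but the sample size section does not. If 288 holds no allowance for that correlation, the stated 80% rests on a smaller variance than the planned model will have. The assurance of adequate power also rests on patient numbers alone, while the number of sites is fixed at 16. Beyond a point, more patients per site add almost no information about a site-level intervention.

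At stake is how a null result would be read. It would come from a study described as well powered, when its actual power depends on a quantity the sample size section never mentions.

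**Working it through.** **Inputs from the article.** 5% v 15% (the 10% change read as absolute); alpha 5%; power 80%; non-response 25%; 144 per arm; 8 sites per arm. This gives 144/8 = 18 recruited per site, and 18 × 0.75 = 13.5 analysed per site (108 per arm). Ten admissions a week for 26 weeks gives 260 per site, or 2,080 per arm.

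**Assumption.** The article gives no ICC. The range 0.01 to 0.10 is assumed.

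**Step 1: reproduce 288.** Two-proportion formula for independent patients:

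n per arm = [z_α √(2 × 0.10 × 0.90) + z_β √(0.05 × 0.95 + 0.15 × 0.85)]² / 0.10²

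| Reading | n per arm | After 25% non-response | Total |
|---|---|---|---|
| One-sided 5%, with non-response | 111 | 111/0.75 = 148 | 296 |
| Two-sided 5%, no non-response | 141 | not applied | 282 |
| Two-sided 5%, with non-response | 141 | 141/0.75 = 188 | 376 |

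The first two are within 3% of 288; the third is not close. Both readings that match use independent patients and leave no room for a design effect.

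**Step 2: power at 288 with clustering.** Design effect = 1 + (m − 1) × ICC, effective n per arm = 8m / design effect, and

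power = Φ{[0.10 √n_eff − z_α √0.18] / √0.175}

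Example, two-sided, m = 18, ICC 0.05: design effect 1.85; n_eff = 144/1.85 = 77.8; (0.882 − 0.832)/0.418 = 0.12; power 55%.

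| ICC | One-sided, 108 per arm | Two-sided, 144 per arm | Two-sided, 108 per arm |
|---|---|---|---|
| 0 | 79% | 81% | 69% |
| 0.01 | 75% | 75% | 64% |
| 0.02 | 71% | 69% | 59% |
| 0.05 | 61% | 55% | 48% |
| 0.10 | 50% | 40% | 37% |

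The first two columns are the readings that match 288. The third takes alpha as two-sided and also applies the stated 25%. Its shortfall at ICC 0 (69% against 80%) is a separate problem, not due to clustering.

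**Step 3: power if all 260 admissions per site are analysed (two-sided).**

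| ICC | Design effect | n_eff per arm | Normal | t on 14 df |
|---|---|---|---|---|
| 0.02 | 6.18 | 337 | 99% | 98% |
| 0.05 | 13.95 | 149 | 82% | 78% |
| 0.10 | 26.9 | 77 | 55% | 50% |

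The 14 degrees of freedom are 16 sites minus 2.

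**Step 4: the ceiling.** As m grows, n_eff per arm tends to 8/ICC and cannot exceed it. Two-sided 80% needs 141, so ICC must be at most 8/141 = 0.057 (about 0.050 with t on 14 df). One-sided, 8/111 = 0.072. Above these values no number of admissions reaches 80%. At 260 per site, the largest ICC that keeps 80% two-sided is 0.053 (normal) or 0.047 (t).

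**The case against.** The strongest reply is that 288 is only a minimum and the audit covers all admissions, so 13.5 or 18 per site understates the data. This stands. With 260 per site, power is well above 80% at an ICC of 0.02. With a quarter of that volume (65 per site), two-sided normal power is still 95% at 0.02. A reader might infer that the study as it will be run is underpowered, or that extra admissions do nothing. The documents support neither. They support only that admissions do not guarantee power. Against the reply, 260 counts admissions rather than eligible patients, so it is an upper figure at the stated rate.

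The upper end of the ICC range can also be challenged. At 5% prevalence, ICC 0.10 implies a between-site SD of √(0.10 × 0.05 × 0.95) = 6.9 percentage points, against 3.1 at ICC 0.02. Pair-matching and the baseline audit could also reduce unexplained site variance. Both points are fair. The article quantifies none of this, so they argue for stating an ICC, not for omitting one.

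A reader might blame clustering for the whole drop from 80% to 64% at ICC 0.01 in the two-sided, 108-per-arm column. That is wrong: 11 of those 16 points are already lost at ICC 0.

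A reader might also infer from the shared nurse that there are only four independent units per arm. The documents do not support this. Control sites have no facilitator, and nothing says that control wards share a hospital.

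**Conclusion.** The point holds as a defect in the stated sample size and power. The 288 contains no allowance for clustering, although allocation is by site and the analysis models it. Under the two readings that match 288, power at that number is 75% at an assumed ICC of 0.01, 69-71% at 0.02, 55-61% at 0.05 and 40-50% at 0.10.

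The near-certainty about power does not follow from admission rates. It is justified if the ICC is low and most admissions are analysed, borderline near 0.05, and unattainable two-sided above about 0.05 to 0.057 with 8 sites per arm. Roughly even odds of detecting the target effect applies at the full admission volume only near ICC 0.10.

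The planned analysis is not invalidated, since it accounts for site clustering; the fault is an overconfident power statement. The Discussion repeats it and extends it to cost-effectiveness, for which the article shows no power or precision calculation.

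These figures rest on the assumed ICC range, equal site sizes, 5% v 15% and no gain from matching or adjustment.

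**What to change.** 1. In the sample size section, state whether alpha is one- or two-sided, and make 288 agree with that choice and the 25% non-response.
2. Restate power for 8 sites per arm over an ICC range such as 0.01 to 0.10, giving the reason for the range. Use the number of records per site that the audit will analyse and a small-sample t reference.
3. Say that power depends on the ICC and the number of sites, not on admission volume alone.
4. Replace the closing assurance of that section with the recalculated figures, or delete it. Do the same with the power claim in the Discussion, including its extension to cost-effectiveness.

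The cost is a recalculation, some rewording and a less favourable stated power. No extra patients or sites are needed.

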### Intervention

The intervention, ACP, is offered as part of routine service to the patients who are admitted to participating intervention wards/community centres. The intervention is a series of facilitated conversations about the components of ACP between people with chronic diseases, their SDMs and RN ACP facilitators.

#### Conversation 1

On admission, as a routine service, people with chronic diseases (and/or family if present) in intervention wards/community centres will be given a one-page ACP Brochure (produced by NSW Ministry of Health - Making your wishes known) by admitting Medical Officer (MO) &/or admitting Registered Nurse (and Social Worker if applicable).

#### Conversation 2 and more

All people with chronic diseases and their nominated SDMs who meet the inclusion criteria will be assessed by RN ACP facilitators for English Proficiency, cognitive impairment and acute episode of mental illness by asking the following questions as recommended by NSW Planning Ahead Tools [5].Do you remember and/or understand the ACP brochure given by MO or RN or SW?,Who should your doctor talk to about your medical treatment?You have a choice to have or not to have a conversation(s) with me. Do you want to have a conversation(s) with me?

RN ACP facilitators will begin with open ended questions exploring the person’s knowledge, attitude and desire to participate in ACP. RN ACP facilitators will also clarify the person’s goals and values; identification of whom should be involved in these conversations; and the person’s understanding of diagnosis, prognosis and preferences for treatment options and place of care.

According to responses, RN ACP facilitator will initiate and facilitate a series of conversations between person, the nominated SDM, treating medical team, and/or a Health Care Interpreter or appropriate Cultural Support Person if required. The components of ACP include personal details, Person Responsible, personal values about dying, directions about medical care, specific requests for organ and tissue donation, and authorisation with signatures in Section 1 to 5 in NSW Ministry of Health ‘Making an ACD’ [5]. A summary of outcomes of these conversations will be entered: 1) in the person’s medical record; 2) A Conversation Log; and 3) A ‘Conversation card’ which is a size of business card when folded and which will be carried in participating patient’s wallet/purse.

Ongoing commitment from participants is not required. The series of conversations are optional and consent to proceed will be checked repeatedly through the course of discussion. The post-evaluative surveys and interviews are also voluntary and are ‘one-off’ so do not involve ongoing follow up or appointment. All potential participants will have as much time as they require to consider participation, but at least 24 h between provision of information (written information statement and verbal explanation) and gaining written informed consent for participation is recommended in line with the National Statement on Ethical Conduct in Human Research [23] and Good Clinical Practice guidelines [24].

### Data collection

#### Audit of ACP related practice

Data on the prevalence of ACP and ACDs will be collected through an audit of the medical records of patients admitted to the 16 research sites within the following time frames:The two month period before the introduction of the intervention period,The six month period of the intervention

The audit will initially check for the presence or absence of evidence of ACP only. Then the individuals whose medical records contain evidence of ACP will be invited to consent to access the content of ACDs (or documentation detailing personal values or specific wishes relating to medical care &/or organ donation). The audit involves the following steps.Medical records from all individuals admitted to a research site at the given times will be requested from relevant medical records departments. Records will be audited for the presence or absence of ACP only.Medical Record Numbers (MRN) of those containing evidence of ACP will be recorded. They will then be posted a letter of invitation and consent form with a pre-paid, self-addressed envelope.The individuals will return the consent form directly to the Research team. Where a completed consent form is returned, the individuals’ medical records will be re-accessed to collect information to assess the quality and completeness of any ACP or ACD, and whether there is concordance of care with the individuals expressed wishes, values and beliefs.

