**Methods:**

The aim of this study is to investigate the effects of normalising ACP in acute and community settings with the use of specially trained normalisation agents. This is a quasi-experimental study, involving 16 sites (8 intervention and 8 control) in two health districts in Australia. A minimum of total 288 participants will be recruited (144 intervention, 144 control). We will train four registered nurses as normalisation agents in the intervention sites, who will promote and facilitate ACP discussions with adult patients with chronic conditions in hospital and community settings. An audit of the prevalence of ACP and Advanced Care Directives (ACDs) will be conducted before and after the 6-month intervention period at the 16 sites to assess the effects of the ACP service delivered by these agents. We will also collect interview and survey data from patients and families who participate, and healthcare professionals who are involved in this service to capture their experiences with ACP.

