**Fig. 1 Fig1:**
[figure not shown]
Research flow chart

ACP will be normalised into practice for 6 months by RN ACP facilitators (normalisation agents) in nominated wards/units in acute and community settings in two Local Health Districts (LHDs). Pre and post measures (the number of people who have ACDs in medical records, Resuscitation plan, any records or notes about ACP discussion and documentation, and the concordance between the expressed wishes and the care delivered) will be obtained for the two groups. Post qualitative data (textual data, individual/focus group interviews with patients, SDMs and staff participants) will be collected and inform the challenges, strategies and implications for future policy and practice.

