### Data analysis

#### Qualitative data collection & analysis: audio-recorded individual/focus interviews

Qualitative data will be collected through audits, surveys, individual interviews and/or focus groups for both baseline and post-intervention. Content of Individual/Focus Interviews will be audio recorded (if consent given) and will be transcribed to text. Textual data will be broken down, line-by-line, and open coded i.e. specific categories relevant to the research aim and questions will be pre-identified and labelled but new categories and sub-categories will be added during analysis. Open codes will be systematically inspected and scrutinised in relation to a ‘paradigm model’ in NTP. With the research aims and questions in mind, the analysis will focus on the agents (who), coherence in conditions or context (where, when, why), coherent/collective actions/interactions (process) and reflexive monitoring (e.g. outcomes). NVivo Software will be used to handle the large amount of data.

Textual analysis (directed content analysis) will be undertaken on the following:Transcripts of interviews with people with chronic diseases & SDMsTranscripts of Individual/Focus Interviews with healthcare professionals (MO, RN, SW, RN ACP Facilitator)Completed open-ended questions from Surveys of people with chronic diseases & SDMs, healthcare professionals (MO, RN, SW, RN ACP Facilitator).

Directed content analysis will also be undertaken on information collected/recorded during delivery of the research intervention (facilitated conversations documented in medical notes and on a ‘conversation log’ and potential completion of a ‘conversation card’ and other ACP related documents, as follows:Questions, concerns, comments, reasons for uptake and refusal of the service (i.e. reasons for consenting to, or declining participation in the study).What participants already know [about ACP], and want to know.The extent and the recorded reasons for discordance [between patients’ and SDMs’ expressed wishes and the actual care they received].The experiences of patients and SDMs with ACP.The experiences of ‘normalisation agents’ [MOs, RNS &/or SWs and RN ACP Facilitators].

The reporting of qualitative measures will follow the Standards for Reporting Qualitative Research (SRQR) [25].

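### The all-records audit scores only presence or absence of ACP, so facilitators' own notes can raise ACP prevalence at intervention sites without one extra completed ACD

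*Protocol article*

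**What the plan says.** Five parts of the protocol article bear on this.

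- **Purpose of the audit** (Abstract, Methods). The audit before and after the six-month intervention is there "to assess the effects of the ACP service delivered by these agents".
- **Measures** (Design, text after Fig. 1). The pre/post measures for both groups are ACDs in the medical record, resuscitation plans, concordance of care with wishes, and "any records or notes about ACP discussion and documentation".
- **Audit steps** (Data collection, Audit of ACP related practice). The section opens by saying that it will measure how common both ACP and ACDs are. It then restricts the pass over all records twice: "The audit will initially check for the presence or absence of evidence of ACP only", and "Records will be audited for the presence or absence of ACP only". Content, quality and completeness of an ACD are read later, only in people whose record was positive and who post back a consent form. The windows are the two months before the intervention and the six months of the intervention itself.
- **Documentation duty** (Intervention, Conversation 2 and more). "A summary of outcomes of these conversations will be entered: 1) in the person’s medical record", as well as in a log and on a wallet card. Only intervention sites have facilitators.
- **Primary outcome** (Sample size calculation). The outcome is "that being the proportion of completed NSW ACDs". The Health economic evaluation also takes completed ACDs as the effect.

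**The concern.** A facilitator's summary is itself evidence that ACP took place. It is written as part of the study service, in one arm only, into the document that the audit reads, and during the months that the audit reads. A patient who had one conversation and completed nothing can turn the record positive. Control sites have no counterpart to this source of notes. Comparing change from baseline between arms does not remove it, because the notes are absent from the intervention arm at baseline and appear only at follow-up.

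Two things are at stake. First, a difference in ACP prevalence could be read as changed practice when part or all of it is study nurses recording study conversations. Second, the only variable that the audit steps define for every record is this mixed one. Records are re-opened only for people who return consent, so an ACD item not captured at the first pass cannot readily be recovered later for everyone.

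**Working it through.** **The plan's own figure.** The sample size section gives 144 per group for a rise from 5% to 15%, with alpha 5%, power 80% and 25% non-response. With a one-sided test and unpooled variance:

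n = (0.05 × 0.95 + 0.15 × 0.85) × (1.645 + 0.842)² / 0.10² = 108.2, and 108.2 / 0.75 = 144.3.

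This agrees with 144 to the nearest integer. A two-sided test with pooled variance needs 141 before inflation and 141 / 0.75 = 188 after it. Sidedness is a separate matter. Here I need only the planned 10-point change and the 144 per group.

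**Inputs for the illustration**

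- ACD prevalence of 5% in both arms at follow-up, meaning no effect on ACDs. The 5% is the protocol's assumed baseline for completed ACDs; that it stays there is my assumption.
- u = share of the other 95% of intervention-site records that hold a facilitator note but no ACD. Assumed.
- c = share of the other 95% of control records that hold an ACP note but no ACD. Assumed; the documents give no such rate.

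**Formulas**

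- Evidence of ACP, intervention = 5% + 95% × u
- Evidence of ACP, control = 5% + 95% × c
- Difference = 95% × (u − c)

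With c = 0, a 10-point difference needs u = 10 / 95 = 10.5%.

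**Results.** The last column is the chance of two-sided p < 0.05 at 144 per group, ignoring clustering.

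| c | u | Intervention | Control | Difference (points) | Chance of significance |
|---|---|---|---|---|---|
| 0 | 5% | 9.75% | 5% | 4.75 | 34% |
| 0 | 10% | 14.5% | 5% | 9.5 | 78% |
| 0 | 20% | 24% | 5% | 19 | 99.7% |
| 0 | 30% | 33.5% | 5% | 28.5 | about 100% |
| 10% | 10% | 14.5% | 14.5% | 0 | not applicable |
| 10% | 20% | 24% | 14.5% | 9.5 | 53% |
| 10% | 30% | 33.5% | 14.5% | 19 | 97% |

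Every non-zero difference in the table arises with no extra ACD. Allowing for clustering by site would lower the chances of significance but would not change the differences.

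**Is a separate ACD count provided?** The Design section lists ACDs as their own measure, and the opening of the audit section names them. The numbered steps do not carry this through. The all-records step yields one presence/absence result for ACP, and the ACD itself is examined only after consent. A proportion of completed NSW ACDs with all audited records as its denominator cannot be built from those steps as written.

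**The case against.** The strongest reply is that the named primary outcome is completed NSW ACDs, and a conversation note cannot create one. That stands: if ACDs are counted separately, the primary outcome is not inflated, and a reader should not infer that it is.

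A second reply is that the restriction in the audit section may separate presence or absence, which needs no consent, from content, which does, and need not mean a single merged flag. That reading is possible, and the audit form is not shown. But the article states the restriction twice, in terms of ACP alone, and never says that ACDs are ticked separately at that pass. This is wording that conflicts with the Design section, not detail left to a fuller document.

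A third reply is that documented conversations are a legitimate thing to measure. The Aims include how far planning is initiated, discussed and documented, and Table 1 counts the facilitators among the normalisation agents. This also stands. It is a reason to report facilitator notes, but not to merge them into a between-arm effect without showing the result that leaves them out.

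Finally, a reader might infer that patients who declined are also scored positive, because the qualitative analysis draws on "reasons for uptake and refusal of the service". The documents do not support this. The intervention section asks for summaries of conversations, the reasons for refusal may sit in the conversation log rather than the medical record, and nothing says that a refusal counts as evidence of ACP.

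**Conclusion.** The point holds for the ACP-prevalence comparison. Followed as written, the plan lets delivery of the intervention raise that measure in one arm. With ACDs at 5% in both arms and no note-only records at control sites, facilitator notes in about 10.5% of the other intervention-site records reproduce the planned 10-point change. If 10% of the other control records also carry an ACP note, 20% coverage is needed for a 9.5-point difference. Coverage, the control note rate and the absence of any ACD effect are assumptions; the 5% is an ACD baseline, not a documented rate of ACP evidence at control sites.

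It does not hold that the ACD outcome is biased upward. The defect there is that the audit steps give no ACD count for all records, although the design, the sample size and the economic evaluation rely on one. One might also infer that people invited to the consented review at intervention sites will mostly have only a facilitator note. That follows from assumed coverage combined with an assumed zero ACD effect, and the documents establish neither.

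**What to change.** In the audit section, replace the single ACP result with four yes/no items, taken from every audited record in both arms and both periods:

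- (a) completed NSW ACD on file;
- (b) resuscitation plan;
- (c) ACP note by usual-care staff;
- (d) ACP note by a study facilitator.

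Compare arms on (a) as the primary outcome and on (b) and (c) as secondary measures. Report (d) separately as reach or process. If (d) is also pooled into an overall ACP-prevalence effect, show beside it the result that excludes (d). Align the list of measures in the Design section with these items.

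The plan currently places the reading of completeness after consent. It should therefore state what marks a form as completed for item (a), and confirm that noting this belongs to the unconsented step.

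The cost is a few more audit fields, the need to identify who wrote each note, and a less favourable ACP-prevalence figure. No extra patients or staff are needed. The change should be made before the first pass, since records are re-opened only with returned consent.
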